### Sample size calculation

A sample size calculation was completed to estimate the number of schools needed for the trial. The calculation was based on our primary outcome of the percentage of time students spent in MVPA during PE lessons. Based on Lonsdale et al.’s meta-analysis [14], the expected standardized difference, or Cohen’s *d*, between intervention (using fitness infusion strategies) and control groups was 1.4. Using a more conservative estimate, we used *d* = 0.9 for our sample size calculation. Calculations were conducted using GPower 3.1.7, with an alpha level set to .05 and power to .80. The required sample size was calculated to be 42. In the current trial, each class would be treated as an individual cluster. Therefore, the calculated sample size was then multiplied by a design effect of 1 + (*m* – 1)ρ, where *m* represents the cluster size (estimated to be 30) and ρ is the intraclass coefficient (ICC). Based on a study conducted in Hong Kong [17], the ICC was estimated to be at .60. Therefore, the final number of participants required was 42 × [1 + (30-1) × .60] = 773, meaning a total of 26 schools will need to be recruited.

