### Randomization

Randomization will take place after baseline measures are taken. A matched-pair randomization protocol will be used. Specifically, the classes will be paired based on (1) class sex (mixed versus female versus male), (2) school type (mixed or single-sex), (3) class size (inclusive of non-participating students), (4) average family income (low versus mid versus high; to be reported by school teacher), and (5) the percentage of MVPA during PE measured at baseline. Each class will then be assigned a computer-generated random number. In each matched pair, the class with the larger assigned number will be allocated in the experimental group, while the other class will be assigned to the control group.

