### Statistical analyses

The primary outcome to be evaluated in the trial is students’ percentage of time spent in MVPA during school PE. Secondary outcomes include percentage of time spent in leisure time MVPA, perceived need support from teachers, need satisfaction, autonomous motivation, psychological well-being, and intention to engage in physical activity. To account for the clustering nature of data, multilevel analyses will be used. Specifically, for each outcome, a three-level (time within student within class) model will be evaluated. Analyses will be conducted using MLwiN v2.26 [52]. For all outcomes, the effectiveness of the intervention will be examined through the multilevel regression equation:$$ \mathrm{Outcome}=\mathrm{B}0+{\mathrm{Gender}}^{\ast}\mathrm{B}1+{\mathrm{Age}}^{\ast}\mathrm{B}2+{\mathrm{Group}}^{\ast}\mathrm{B}3+{\mathrm{Time}}^{\ast}\mathrm{B}4+{\mathrm{Group}}^{\ast }{\mathrm{Time}}^{\ast}\mathrm{B}5 $$

Specifically, the intervention will be considered to be effective in promoting the outcomes if the Group*Time term is positive and significant at *p* < .05.

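### The stated power of .80 belongs to a one-time-point comparison, not to the Group*Time test that decides effectiveness. The power of that test depends on a correlation the protocol does not give.

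*Protocol article*

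**What the plan says.** Under Sample size calculation the protocol article states: "The calculation was based on our primary outcome of the percentage of time students spent in MVPA during PE lessons". The effect is a between-group standardized difference: "Using a more conservative estimate, we used *d* = 0.9 for our sample size calculation". The test is set up "with an alpha level set to .05 and power to .80", and "The required sample size was calculated to be 42". This is multiplied by a design effect for classes of 30, where "the ICC was estimated to be at .60", to give 773 students and 26 schools. No baseline, repeated-measures or change-score correlation enters.

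Under Randomization: "Randomization will take place after baseline measures are taken". Classes are paired on five factors, one of which is baseline PE MVPA, and allocation is random within pairs.

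Under Statistical analyses the model has three levels (time, student, class) and fixed terms for gender, age, Group (B3), Time (B4) and Group*Time (B5). The decision rule is that "the intervention will be considered to be effective in promoting the outcomes if the Group*Time term is positive and significant" at the 5% level. Neither the matched pair nor baseline MVPA appears as a covariate, and no class-by-time random effect is named.

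**The concern.** The sizing and the decision rule describe different tests. The sizing compares two arms on the level of MVPA once. The decision rule compares the change in MVPA between arms, because B3 lets the arms differ freely at baseline. Randomization after baseline makes that difference zero in expectation, so estimating it costs precision and corrects no bias.

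The precision of a difference in change depends on how strongly class means at baseline predict class means at follow-up. If they predict weakly, subtracting baseline adds noise, and the planned test can be weaker than one that ignores baseline. With 26 randomized units, the stated power could be well off in either direction. Nothing in the article lets a reader tell which.

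**Working it through.** **Inputs.** From Sample size calculation: d = 0.9, alpha .05, power .80, m = 30, ICC = .60, 26 classes (13 per arm). Not in the document and therefore assumed: r, the correlation of class means between the two time points, taken over .1 to .7.

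**Reproducing the plan's figures.** A two-sided two-sample t-test with d = 0.9 has power .792 with 20 per arm and .812 with 21 per arm, hence 42. (A one-sided test would need 32.) The design effect is 1 + 29 × .60 = 18.4. Then 42 × 18.4 = 772.8, rounded to 773, and 772.8 / 30 = 25.8, rounded to 26. The figures are correct for a single comparison at one time point.

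**Class-level power.** With total student variance set to 1, a class mean has variance 18.4 / 30 = .613. For one time point the noncentrality is .9 / √(2 × .613 / 13) = 2.93, which on 24 df gives power .803.

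Relative to that, the variance of each estimate is multiplied by:
- Group*Time with a free baseline difference: 2(1 − r)
- Baseline-adjusted: 1 − r²

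Dividing 2.93 by the square root of the factor gives the noncentralities below (24 df for Group*Time, 23 df for adjustment).

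| r | Group*Time: noncentrality | Group*Time: power | Adjusted: noncentrality | Adjusted: power |
|---|---|---|---|---|
| .1 | 2.18 | 55% | 2.95 | 81% |
| .3 | 2.48 | 66% | 3.07 | 84% |
| .5 | 2.93 | 80% | 3.38 | 90% |
| .7 | 3.78 | 95% | 4.10 | 98% |

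These figures treat allocation as unrestricted and assume a standard error that reflects class-by-time variation.

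**Allowing for the matching.** The check was repeated by simulation, with 26 classes sorted on baseline MVPA and paired. This is the closest possible matching on baseline, since the plan also matches on four other factors. The true variance of the Group*Time estimate was then only about 1.04, 1.02 and 1.01 times that of the adjusted estimate at r = .1, .3 and .5. The Group*Time standard error, computed without the pairs, stays too large. Power at r = .1, .3, .5 and .7 was:
- Group*Time, pairs ignored: about 57%, 69%, 84% and 96%
- Baseline-adjusted: about 81%, 83%, 90% and 97%
- Baseline-adjusted plus fixed pair effects (11 df): about 73%, 76%, 84% and 95%

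Repeat runs agreed to within about two percentage points.

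**If only random intercepts are fitted.** Class effects that are constant over time imply r of about .60 / .613 = .98, with power near 100%. If class effects in fact shift between semesters, such a model rejects in more than 90% of trials at d = 0.9, but its type I error is about .6 at low to moderate r. That high rejection rate would reflect an invalid test, not good power.

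**The case against.** The strongest reply is that no shortfall is demonstrated. The article gives no r, and above .5 the planned test exceeds its stated power. Stable features of a class (the same students, space and equipment) and the averaging of three lessons could push r up. Lesson content that varies between semesters could push it down. The document settles neither. This stands, and a reader who infers that the trial is underpowered goes further than the text allows.

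A second reply is that the unmatched formulas overstate the loss of precision. They give a variance ratio of adjusted to change of (1 + r)/2, a 35% reduction at r = .3. A reader might quote that as the gain from adjustment, but under close matching on baseline it falls to about 2%. This also stands. What survives is that the written model does not use the matching, so its standard error is too large and power is still lost.

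Third, the power figures assume class-by-time variation is modelled, which the article does not say. This is correct and is a stated assumption here. The random-intercept reading is no defence unless class effects really are stable.

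Fourth, the effect size was deliberately cautious. At the d = 1.4 taken from the cited meta-analysis, the same Group*Time formula gives 87% power at r = 0 and 96% at r = .3. This is a real margin, but the power claim in the article is made at 0.9.

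Finally, Group*Time after randomization is an unbiased and common contrast. The choice here concerns efficiency and the accuracy of the power statement, not validity. It is also possible that d and the ICC were meant for change scores, which would remove the mismatch, but the text defines the calculation on percentage MVPA itself.

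**Conclusion.** The point holds in a limited form. The .80 is the power of a comparison that the plan does not use for its decision. The power of the Group*Time test is unknown without r. Over r = .1 to .7 it runs from about 55% to 95% under unrestricted allocation, and from about 57% to 96% with close baseline matching that the analysis ignores. Baseline adjustment has higher power at each of these values, by some 26 percentage points at r = .1 and 2 to 3 at r = .7 without matching. With close matching the gap is about 24 points at r = .1 and 1 point at r = .7.

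These figures rest on d = 0.9, 13 classes per arm, m = 30, ICC = .60, and a standard error that reflects class-by-time variation. They do not show that the trial is underpowered.

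**What to change.** Make the primary analysis a multilevel model of follow-up PE MVPA on group, adjusted for the student's baseline PE MVPA and the class baseline mean, with gender and age as planned. Alternatively, keep the long format, drop B3 so that the arms share one baseline mean, and include a class-by-time random effect.

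Do not add fixed matched-pair effects on top. They leave about 11 df and bring power down to about 73%, 76%, 84% and 95% at r = .1, .3, .5 and .7.

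Restate the power for the test actually used, at 26 classes, over a stated range of r.

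The cost is one class-level degree of freedom (at r = 0, .801 against .803 for a follow-up-only comparison) and a revised equation and power sentence. No extra schools or data are needed.

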### Teacher and student interviews

After all quantitative follow-up data are collected, qualitative interview data will be collected from teachers and students. Through individual or focus group interviews, we aim to acquire subjective reflections of teachers’ and students’ view on the intervention. More specifically, we will ask teachers and students how they compared the fitness dice activity to usual fitness activities teachers had been using. Subjective reports on changes in activity levels and teacher behaviors before and after the intervention will be sought from both teachers and students. Example questions include whether students enjoyed the fitness dice activities, whether their activity levels changed as a result of using the dice, or whether there were changes in teacher behaviors after the fitness dice were used (i.e., after the first teacher workshop). The full interview schedule will be provided upon request from the first author.

## Discussion

The SELF-FIT intervention has been designed to increase students’ MVPA during PE lessons and enhance their motivation for fitness activities. By combining approaches that are aimed to modify teacher teaching strategies and interpersonal styles, and modifications to fitness activity selection during PE, we aim to make students perceive fitness exercises to be more fun and engaging. The SELF-FIT intervention is innovative because previous PE interventions have manipulated teachers’ behaviors or infused fitness activities into existing classes, but not both. Instead, as previously suggested [17], in our intervention, modifications to teacher behavior *and* fitness infusion methods are applied, while SDT tenets where integrated into both sets of strategies. Therefore, we expect the intervention will positively impact students’ MVPA and autonomous motivation for PE.

The effects of existing school-based fitness infusion intervention may be difficult to carry over to students’ leisure time, because vigorous activity in itself may not be perceived as enjoyable [53]. However, by infusing game play elements and designing the intervention based on SDT, we aim to enhance students’ motivation for physical activity, which may in turn lead to increases in leisure time activity behaviors. For example, we will suggest that teachers implementing the intervention allow students to design their own fitness activities for the fitness dice. This may encourage students to spend additional time on fitness activities outside PE or raise their interest in these exercises. In addition, this will help students take more ownership of activities within PE. The intervention may expose students (and even teachers) to a larger variety of fitness activities, and thereby enhancing their knowledge, which may be linked to future (re-)engagement in similar activities.

Apart from physical activity behaviors, research has shown that there are secular declines in health-related fitness in adolescents across the globe (e.g., [54, 55]). As physical fitness may be related to lower rates of non-communicable diseases, this decline is alarming. Using a train-the-trainer approach, and also relatively cheap equipment (i.e., the fitness dice), the scale of the SELF-FIT intervention could be increased at a relatively low cost. Scalable interventions, such as SELF-FIT, are needed to improve adolescents’ fitness, health, and motivation for physical activity.

## Abbreviations

ICC: Intraclass coefficient
MVPA: Moderate-to-vigorous physical activity
PE: Physical education
SAAFE: Supportive, Active, Autonomous, Fair and Enjoyable
SDT: Self-determination theory
SELF-FIT: Self-determined Exercise and Learning For FITness
